# List of abbreviations

| AE | Adverse Events |
| --- | --- |
| CFS | Clinical Frailty Scale |
| CRF | Case Report Form |
| CRP | C-Reactive Protein |
| DAH | Days alive and out of hospital |
| DSMC | Data Safety and Monitoring Committee |
| EPO | Erythropoietin |
| ESR | Erythrocyte Sedimentation Rate |
| EQ-5D-5L | European quality of Life – 5 dimensions – 5 levels |
| GCP | Good Clinical Practice |
| GMP | Good Manufacturing Practice |
| Hb | Haemoglobin |
| HIF | Hypoxia-inducible Factor |
| HREC | Human Research Ethics Committee |
| IP | Investigational Product |
| ISF | Investigator Site File |
| I.V. | Intravenous |
| MCV | Mean Corpuscular Volume |
| PI | Principal Investigator |
| PH | Prolyl Hydroxylase |
| PICF | Participant Information Sheet and Consent Form |
| PMG | Project Management Group |
| QoL | Quality of Life |
| RBC | Red Blood Cell |
| RDW | Red cell Distribution Width |
| SAE | Serious Adverse Event |
| SOP | Standard Operating Procedure |
| SST | Serum separator tube |
| STFR | Soluble transferrin receptor |
| SUSAR | Suspected Unexpected Serious Adverse Reaction |
| TGA | Therapeutic Goods Administration |
| TSat | Transferrin Saturation |
| TSC | Trial Steering Committee |

# Abstract

**Background**

Iron deficiency is the commonest nutritional deficiency globally, affecting 2 billion people and is the leading cause of anaemia. Iron deficiency anaemia makes people tired and unwell as well as impacting physical function, it is a WHO top 10 leading cause for disability. (1, 2) Anaemia is common in patients undergoing major surgery and associated with worse patient outcomes (3-5) and increased post operative mortality. (3, 5-7)

The aetiology of anaemia in the surgical patient is multifactorial; it can be related to co-morbidities and chronic disease, the illness or problem for which the patient is undergoing surgery, blood loss at operation or secondary to surgical inflammation. However, the mechanism of anaemia in surgical patients is not clear. Hepcidin, the master regulator of iron homeostasis, impacts iron absorption and cellular transport by regulation of the main iron transport protein (Ferroportin). Upregulation of Hepcidin by Cytokines (particularly IL-6) leads to a functional iron deficiency as iron transport in the reticuloendothelial system is impaired due to sequestration of iron into macrophages. If prolonged this can lead to anaemia of chronic disease. Conversely, blood loss inhibits hepcidin to promote iron absorption and transport to the bone marrow, but post operatively it is unclear how recovery of anaemia and hypoxic drive for erythrogenesis is impacted by this inflammatory modulation.

The aim of this trial is to explore the mechanisms of iron deficiency over the perioperative time period in patients undergoing cardiac, abdominal and vascular surgery and the response to intravenous iron therapy that bypasses the normal Hepcidin mediated iron pathways. Secondary aims include to assess the efficacy of intravenous iron and feasibility of measuring potential effects on patients’ physical recovery.

**Methods**

AMBLE will be a prospective, parallel-group, double blinded, 2 by 2 factorial, randomised, multi-centre trial designed to investigate iron deficiency in cardiac, abdominal, and vascular surgery patients. Potential participants will be identified through normal clinical pathways for surgery and anaesthesia such as surgical outpatient and preoperative clinics, surgical admissions, or inpatient wards. The Perioperative group will assess the mechanisms of iron deficiency and response to intravenous iron therapy in the perioperative period. The Recovery group will assess feasibility to test patients physical and quality of life recovery in the postoperative setting and assess if this differs between iron deficient and iron replete patients.

Two separate groups of patients will be assessed:

- The Perioperative group of patients included if about to undergo major cardiac, abdominal and vascular surgery to assess the mechanisms of iron deficiency in the perioperative period.
- The Recovery group of patients included 4 weeks after hospital discharge following major cardiac, abdominal and vascular surgery to assess recovery of physical function and anaemia.

Following screening, participants who provide informed consent will undergo baseline blood tests, quality of life (QoL) questionnaires and functional assessments. Following this, participants will be randomised to either an intravenous iron administered either directly post-operatively in the Perioperative group or 4 weeks post operatively in the Recovery group, or placebo.

Follow up assessments will occur:

- The Perioperative group at Days 1, 2, 4, 8 and 2 weeks then weeks 4, 8, 12 and 16.
- The Recovery group weeks 4, 8, 12 and 16.

**Discussion**

The outcomes of this research will generate a better understanding of the mechanism of iron deficiency anaemia in surgical patients as well as how this affects post operative recovery. By better understanding the aetiology of iron metabolism in surgery we can determine what intervention (iron +/- EPO) may improve patient outcomes and the administration timing thereof. As a result, more informed decisions will be made regarding iron supplementation and therapy in these patients.

**Keywords** Vascular Surgery, Abdominal surgery, Anaemia, functional outcome, Critical Limb Ischemia, Major Limb Amputation, Major Adverse Cardiac Events

# Introduction

## Background and Rationale [6a]

**Anaemia worsens outcomes for surgical patients:**

Anaemia affects nearly a quarter of the world (6) and is common in surgical patients with a third of patients presenting with preoperative anaemia and three quarters of patients discharged from hospital with anaemia (7). The World Health Organisation defines anaemia as an insufficient circulating red cell mass, with a haemoglobin (Hb) concentration of < 130 g.l−1 for men and < 120 g.l−1 for women (6).

Perioperative anaemia is associated with increased postoperative complications and delayed patient recovery leading to increased post-operative morbidity and mortality (6-12) Anaemia also leads to an increased use of allogeneic blood transfusions (12-15), which is an independent risk for poorer patient outcomes (15-18).

The most common cause of preoperative anaemia is iron deficiency, which can be caused by reduced or impaired dietary iron absorption, chronic blood loss, or disruption of normal iron metabolism due to comorbidities or inflammation, aetiologies commonly seen in patients undergoing major abdominal surgery, which causes an increase in hepcidin production resulting in functional iron deficiency (18-20) and reduced red cell production.

**Clinical trials on intravenous iron:**

The use of intravenous iron has become a normal treatment for anaemia in Australia and supported by international guidelines. (21, 22) We investigated the efficacy of intravenous iron to treat anaemia (23) suggesting efficacy to increase haemoglobin. This was confirmed in our multicentre cohort study of patients before Cardiac and Vascular Surgery which showed efficacy to increase haemoglobin levels but with no patient effect (24, 25). In large multicentre PREVENTT RCT we randomised 487 patients at 46 centres to intravenous iron or placebo 10-42 days before major abdominal surgery. (26) Unexpectedly there was no impact on blood transfusion (29% vs. 28%; p = 0.92) or postoperative complications (24 [11%] vs. 22 [9%]; RR 0.89, 95% CI 0.52 to 1.55; p = 0.69), length of hospital stay (median [IQR]: 9 [7–14] days vs. 9 [5–14] days; p = 0.14), or mortality rate (1% vs. 1%; p = 1.0) These findings were unaffected by subgroup analysis (age, gender, [Hb]) or, on reanalysis, by markers for iron deficiency (ferritin, Tsats).(27)

The NOVEL FINDING in PREVENTT was that the greatest impact from intravenous iron was seen after surgery with a significant rise in [Hb] at 8 weeks (MD: 10·7 g/L; 95% CI, 7·8- 13·7). This efficacy of intravenous iron was associated with a reduced readmission rate to hospital for post operative complications (21.8% to 13.8%; relative risk reduction 29.5-39.4%) and reduced additional bed stay (877 to 299 days).

We confirmed this finding in a large multicentre prospective RACS CTANZ audit of 2730 patients at 56 hospitals in Australia and New Zealand. Preoperative anaemia was seen in 28% of patients undergoing major surgery and associated with an increased risk of transfusion, postoperative complications, reoperation, MET calls, and a longer length of hospital stay (all p<0.001). Importantly, Postoperative anaemia was common (59.2%, 1186/2003), and associated with a higher rate of readmission (13.5% vs. 7.6%, p<0.001). (MJA 2022 in press). (27)

**Understanding the mechanism of iron deficiency in surgical patients:**

Surgical anaemia can be due to chronic disease, blood loss at operation or secondary to surgical inflammation. Cytokines (particularly IL-6) upregulate hepcidin, the master regulator of iron homeostasis, which prevents iron transport leading to failure of dietary iron absorption, and sequestration of iron within macrophages. (28, 29) This leads to functional iron deficiency and subsequently anaemia of chronic disease.

The efficacy of intravenous iron therapy may be impacted by the balance between the inflammatory modulation of iron sequestration and bone marrow suppression with the hypoxic drive for erythrogenesis. Although efficacy of intravenous iron was shown in the IRONMAN trial, we performed in patients following ICU and the PREVENTT trial in preoperative patients, the one size all approach may not be precise. (30, 31) Consequently, in the surgical pathway the optimal timing and modality (intravenous iron +/- EPO) is unknown. Further, with development of disease modifying agents (anti-IL6 therapy or Hepcidin antagonists) and small molecule anaemia therapies with Hypoxia-inducible factor (HIF) prolyl hydroxylase (PH) enzyme inhibitors there is a need to understand the fundamental basis and aetiology of iron deficiency anaemia in the surgical patient.

**Hypothesis:**

Intravenous iron can support erythrogenesis despite post-operative inflammation and improve patient muscle function quality of life and post operative recovery.

# Objectives [7]

## 4.1 Primary Objectives

1. To investigate the pattern and causality of iron deficiency in patients before, during and recovering from major surgery.
2. To investigate the effects of iron deficiency and treatment with intravenous iron and on the functional and mental wellbeing patients during and recovering from major surgery.

## 4.2 Secondary Objectives

Investigate the effect of iron deficiency and anaemia in relation to:

1. Laboratory Outcomes:
   1. Routine Haematology markers of: Hb, MCV, RDW
   2. Routine Iron markers of: Ferritin & transferrin saturations
   3. Experimental Iron markers including: STFR, Hepcidin, Erythroferrone and EPO
   4. Experimental Inflammatory markers including: CrP, IL6 and other cytokines
   5. Proteomic and metabolomic profiles.
2. Mental and physical recovery after surgery
   1. Complications as measured by the Clavien Dindo Scale
   2. Length of hospital stay
   3. Re-operations
   4. Unplanned re-admission to hospital for complications
   5. Days Alive and at Home (DAH) 30 & 90
   6. Clinical frailty score and activities of daily living (Nottingham extended ADL scale)
   7. Sarcopenia as assessed by quantitative skeletal muscle analysis and quantative skeletal muscle changes post intervention (where imaging available)
   8. Functional assessments as assessed by Short Physical Performance Battery; 4 metre gait speed, five time sit-stand test, balance test. Maximal handgrip strength, time to get up and go, or 6-minute walk test
   9. Quality of life measured by SF-36v2 health survey, EQ-5D-5L questionnaire and the POMS questionnaire
3. Adverse events / serious adverse events
   1. Assessment of major adverse cardiac events
   2. Assessment of major adverse limb events
   3. Discharge destination

# 5. Trial Design [8]

Multicentre, prospective, parallel-group, double blinded, 2 by 2 factorial, randomised controlled trial comparing intravenous iron or placebo administration in anaemic patients undergoing major cardiac, abdominal, or vascular surgery.

Perioperative group: Intravenous iron or placebo will be administered immediately post-operatively.
Recovery group: Intravenous iron or placebo will be administered 4 weeks post-operatively.

All patients will be followed for 16 weeks from date of randomisation.

## **6. Study Population [9]**

This study will include patients undergoing cardiac surgery (coronary bypass or cardiac valve surgery), vascular surgery (patients with critical limb threatening ischaemia undergoing open and endovascular revascularisation procedures), and abdominal surgery (patients undergoing major open or laparoscopic procedures). All groups where iron deficiency and anaemia have been identified to be high risk and impact patient outcomes. The comparators will be the interventions before and after randomisation of treatment.

- The Perioperative group of patients included if about to undergo major cardiac, abdominal and vascular surgery will be consented prior to surgery (See Section 7.2)
- The Recovery group of patients included 4 weeks after hospital discharge following major cardiac, abdominal and vascular surgery will be consented post-operatively (See Section 7.2)

The Perioperative group will assess the mechanisms of iron deficiency and response to intravenous iron therapy in the perioperative period. The Recovery group will assess the feasibility to test patients physical and quality of life recovery in the post-operative setting and assess if this may differ between iron deficient and iron replete patients.

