### 11.1.1 Primary Endpoint Change in Hb concentration from baseline to 90 days following randomisation

### 11.1.2 Secondary Endpoints Laboratory:

1. Change in Routine Iron markers
2. Changes in Experimental Iron markers
3. Changes in proteomic and metabolomic profiles.
4. Mental and physical recovery after surgery
5. Complication rate at 30 days post operation
6. Length of hospital stay
7. Re-operations
8. Unplanned re-admission to hospital for complications
9. Days Alive and at Home (DAH) 30 & 90
10. Change in clinical frailty score and activities of daily living (Nottingham extended ADL scale)
11. Changes in Sarcopenia
12. Changes in functional assessments
13. Changes in Quality of life

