## 11.4 Statistical Analysis [20a]

Analyses will be based on all randomised participants. Reporting of research findings will be in accordance with CONSORT guidelines. Baseline demographic data and other participant characteristics will be expressed as means and standard deviations for continuous variables and counts and percentages for categorical variables, with 95% confidence intervals provided for estimates of interest where appropriate. The differences in baseline characteristics will be evaluated by either $\chi^{2}$ or Fisher extract test for categorical variables and an independent samples t-test for continuous variables. Changes in recovery outcome scores will be compared for each participant as the difference between baseline and each specified time points scores with univariate analyses comparing changes in outcome.

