**Methods for additional analyses (e.g. subgroup analyses)**

Each clinical cohort (Cardiac, Vascular and Abdominal surgery) will be assessed in a predefined subgroup.

**Methods in analysis to handle protocol non-adherence and any statistical methods to handle missing data** [20c]

Results will be analysed on an intention-to-treat basis. Secondary analysis will be per protocol.

**Plans to give access to the full protocol, participant level data and statistical code** [31c]

No later than 2 years after the collection of the final 6 month follow up assessments, we will deliver a completely deidentified data set to an appropriate data archive for sharing purposes.

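### Section 6 names the wrong comparator (before versus after randomisation), contradicting the iron-versus-placebo design in section 5, and section 11 never says which arms are compared

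*Protocol*

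**What the plan says.** **Protocol section 5 (Trial Design)** describes the trial as "Multicentre, prospective, parallel-group, double blinded, 2 by 2 factorial" and as a "randomised controlled trial comparing intravenous iron or placebo administration in anaemic patients". Section 11.2 gives the allocation: in each of three surgical cohorts, in both the Perioperative and the Recovery group, 20 patients to iron and 20 to placebo.

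**Protocol section 6 (Study Population)** says: "The comparators will be the interventions before and after randomisation of treatment". The sentence does not mention placebo.

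**Protocol section 11.1.1** gives the primary endpoint as "Change in Hb concentration from baseline to 90 days following randomisation". It names no contrast between arms.

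**Protocol section 11.4** has one sentence on follow-up outcomes. It begins "Changes in recovery outcome scores will be compared for each participant as the difference between baseline and each specified time points scores" and ends "with univariate analyses comparing changes in outcome". It does not say what the changes are compared between. The only between-group test that the section describes explicitly concerns baseline characteristics.

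**The subsection on additional analyses, non-adherence and missing data** adds: "Results will be analysed on an intention-to-treat basis. Secondary analysis will be per protocol".

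**The concern.** The comparator is a design element, and the protocol gives two incompatible versions of it. In section 5 it is a concurrent placebo arm. In section 6 it is the period before randomisation. Section 11 is where a reader would look to settle this, and no sentence there says that an outcome in the iron arm is compared with the same outcome in the placebo arm.

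Hb, physical function and quality of life can all be expected to change after major surgery whether or not iron is given. A before-after contrast within the iron arm measures that natural change plus any effect of iron and cannot separate the two. The randomised comparison can, because natural change is common to both arms and cancels in expectation.

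The SAP may be expected to choose the model. It should not have to correct the comparator: one written from section 6 could adopt a before-after analysis, and one that names placebo would contradict the protocol text.

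**Working it through.** **1. The plan's own figure.** Section 11.2 has no formal sample size calculation, so only the count can be checked: 2 groups × 3 cohorts × (20 + 20) = 240, as stated. Each group has 3 × 20 = 60 iron and 60 placebo patients.

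**2. The statements side by side.**

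| Place | What is compared |
|---|---|
| Section 5 | Iron or placebo, parallel groups |
| Section 6 | Before and after randomisation; placebo not named |
| Section 11.1.1 | Hb change from baseline to 90 days; no contrast named |
| Section 11.2 | 20 iron and 20 placebo per cohort |
| Section 11.4 | Each participant's change in recovery scores, then changes compared; between what is not stated |

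Sections 5 and 6 cannot both be right. Section 11.4 is compatible with either.

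**3. What would follow if section 6 were applied literally.** The protocol gives neither the SD of Hb change nor the spontaneous Hb change to day 90, so both are assumptions.

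- *SD.* Section 3 cites a between-arm Hb difference of 10.7 g/L (95% CI 7.8 to 13.7) at 8 weeks from an earlier preoperative iron trial of 487 patients. SE = (13.7 − 7.8) / 3.92 = 1.505. SD = SE / √(2/n), which is 14.3 for n = 180 per arm and 16.5 for n = 240 per arm. The arm sizes at 8 weeks are assumed, and the result is only a rough guide to the SD of change. I use 15 g/L and show a range of 10 to 17.
- *Spontaneous rise in Hb.* Assumed 3, 5 or 10 g/L.
- *True iron effect.* Zero.

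The test is a one-sample t-test of change in the 60 iron patients of the Recovery group, two-sided 5%, counting only significance in the direction of benefit. Critical value t(0.975, 59) = 2.001. The standard error is 15/√60 = 1.936, and the non-centrality is rise / 1.936.

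| Assumed rise (g/L) | Non-centrality | Probability of a significant benefit |
|---|---|---|
| 3 | 1.549 | 0.33 |
| 5 | 2.582 | 0.72 |
| 10 | 5.164 | 0.999 |

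The nominal rate in that direction is 0.025. With a rise of 5 g/L, varying the SD from 17 down to 10 moves the probability from 0.61 to 0.97.

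**4. The randomised comparison under the same conditions.** In simulation (20,000 runs per setting, no iron effect, 20 or 60 per arm, SD 10 to 17, natural change 0 to 20 g/L), a two-sample t-test of change between iron and placebo rejected in 4.7% to 5.3% of runs. That is the nominal two-sided 5% whatever the natural change.

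**The case against.** The strongest reply is that the rest of the document leaves no real doubt about the intention. The trial is randomised and blinded, with shielded infusions and a specified placebo. Allocation is 1:1, reporting follows CONSORT, and the main analysis is by intention to treat, which presupposes analysis by randomised arm. The closing words of the section 11.4 sentence, "with univariate analyses comparing changes in outcome", can validly mean that change scores are compared between arms. That sentence concerns recovery scores and not explicitly Hb. Using change from baseline is not a fault in itself. The section 6 sentence is also barely coherent taken literally, since no trial treatment is given before randomisation.

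Most of this stands, and it limits the point. A reader might infer that the plan discards the placebo arm, or that natural recovery will be reported as an iron effect. The documents do not support that: they permit the misreading but do not commit to it. A reader might also infer that the bias would run in opposite directions in the two groups, with operative blood loss masking an effect in the Perioperative group. The protocol gives no net Hb change to day 90 for either group, so the sign there cannot be established. For the same reason, a figure that pools the iron patients of both groups under a single assumed rise is not supportable.

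Primary objective 1 concerns the pattern of iron deficiency before, during and after surgery, so describing within-patient trajectories is a legitimate aim.

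What the reply does not remove is the contradiction. To reach the intended comparison, the reader must override a plain statement of the comparator in section 6, and section 11 gives no sentence to put in its place.

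**Conclusion.** The point holds as a misstated design element. Section 6 gives a comparator that contradicts sections 5 and 11.2, and neither the primary endpoint nor section 11.4 names iron versus placebo as the outcome contrast. Any harm depends on the section 6 wording being followed. In that case, with no iron effect, an SD of 15 g/L and a spontaneous rise of 3 to 10 g/L, a before-after test in the 60 Recovery-group iron patients would show a significant benefit in about 33% to over 99% of trials, while the randomised comparison keeps its nominal error rate. The SD and the spontaneous rise are assumptions, so these figures show direction and rough size only. They illustrate the wording and do not predict what the trial will report.

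**What to change.** In section 6, replace the comparator sentence with one that names placebo, for example: *The comparator is placebo; treatment effects are differences between the randomised iron and placebo arms.*

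In section 11.4, state that Hb change to day 90 and the recovery outcomes are compared between the randomised iron and placebo arms, and that before-after changes within an arm are descriptive and not evidence of efficacy. The choice of model can stay with the SAP.

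The cost is a short wording change in a protocol amendment. No new data, visits or patients are needed. It should be made before any unblinded analysis, so that the comparison is fixed without knowledge of the results.
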